## Abstract

**Background:**

Laparoscopic one anastomosis gastric bypass (LOAGB) is a simple variation of gastric bypass and has gained worldwide popularity with clinical outcomes similar to laparoscopic Roux-en-Y gastric bypass (LRYGB) for weight loss and management of comorbidities. However, biliary reflux to the esophagus negates the benefits of LOAGB. In addition, weight gain after LOAGB and after LRYGB is a major problem in bariatric surgery.

The aim of this article is to describe the design and protocol of a randomized controlled trial comparing the outcomes of two methods of LOAGB: experimental method with wrapping versus standard method nonwrapping fundus of the excluded part of the stomach to prevent weight regain and biliary reflux after LOAGB.

**Methods:**

The study was designed as a single-center prospective, interventional, randomized controlled trial. Masking: None (open label). Allocation: randomized. Enrollment: 100 obese patients. The relevant ethics committee approved the trial protocol.

The endpoints (body mass index, bile reflux in the esophagus, other reflux symptoms) will be assessed presurgery and postsurgery (12, 24, and 36 months postoperatively).

**Discussion:**

With its 3-year follow-up time, this RCT will provide important data on the impact of wrapping the fundus of the excluded part of the stomach to prevent weight regain and biliary reflux after LOAGB.

**Trial registration:**

ClinicalTrials.govNCT04834635. Registered on 8 April 2021.

## Administrative information

Data of FundoRingOAGB trial.

## Introduction

### Background and rationale {6a}

Typical early weight loss following bariatric surgery ranges from 47 to 80% of excess weight [1]. However, typical weight regain is 15–25% of that lost weight [2]. Weight regain after surgery is a major problem in bariatric practice. Therefore, adjustable bands and rings are used, such as “FobiRing” for banded gastric bypass [3]. However, foreign material can cause complications, such as erosion of the stomach wall [4]. Therefore, surgeons avoid the use of mechanical devices for banded gastric bypass.

Currently, laparoscopic one anastomosis gastric bypass (LOAGB) or minigastric bypass (MGB) is a common bariatric procedure for treating obesity [5]. The greatest criticism of the LOAGB is for the likelihood of biliary reflux [6]. Biliary reflux resistant to medical treatment has an incidence of 0.6–10% after one anastomosis gastric bypass and may be a reason for revisional surgery [7].

In addition, along with obesity, gastroesophageal reflux disease (GERD) is steadily increasing worldwide, and antireflux surgery must be performed simultaneously with bariatric surgery in obese patients [8]. In these cases, fundoplication may be performed using the fundus of the excluded part of the stomach [9]. Colpaert J et al. reported good short-term results with modified Nissen fundoplication for patients with reflux after RYGB [10]. They opted to perform the same procedure to slow down the passage of food through the gastric pouch. This procedure can be performed as a revision procedure after Roux-en-Y gastric bypass for the treatment of postoperative dumping syndrome [11].

In the literature, we did not find data on the use of a similar method for primary procedures and examples of use for patients without GERD to prevent biliary reflux in one anastomosis gastric bypass and de novo postoperative reflux esophagitis.

### Objectives {7}

We hypothesize that total fundoplication can not only treat GERD but also significantly prevent the return of weight, such as after banded gastric bypass, prevent postoperative bile reflux in the esophagus, and decrease de novo GERD.

The aim of this article is to describe the design and protocol of a randomized controlled trial comparing the outcomes of two methods of LOAGB: the experimental method with wrapping versus the standard method nonwrapping fundus of the excluded part of the stomach.

The main aim of the study are as follows:
Comparing the primary outcome measure: change in body mass index in both groups and weight regain.Comparing the secondary outcome measures: postoperative bile reflux in the esophagus; assessment of GERD if preoperative GERD symptoms (GERD-HRQL) were present or if GERD symptoms occurred postoperatively (de Novo GERD).

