### Outcomes {12}

#### Primary outcome measure

Change of body mass index: The measure assesses a change of body mass index. Weight (kg) and height (cm) will be combined with the body mass index (BMI) kg/m^2^. Time frame: Baseline at 12, 24, and 36 months after surgery. Ideal body weight was calculated as 25 × [patient’s height in meters]^2^. Effectiveness endpoint follow-up included body mass index (BMI, kg/m^2^), change in BMI (ΔBMI [initial BMI − postoperative BMI]), excess BMI loss (EBMIL, % [(ΔBMI/initial BMI − 25) × 100]), and total weight loss (TWL, % [initial weight − postoperative weight/initial weight × 100]).

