## Discussion

Advances in bariatric and metabolic surgery make it possible to include this subspecialty in our national health systems as an independent specialization [17]. LOAGB is recognized as a simple and safe gastric bypass method [12], and LOAGB has been shown to match RYGB in weight loss and metabolic improvement after 2 years [18].

However, the high likelihood of intractable biliary reflux in LOAGB, 2.8% after revisional bariatric procedures (r-LOAGB) and 0.4% after primary LOAGB (p-LOAGB), is a serious complication. A. Soprani et al. [19] collected a series of 16 patients who underwent laparoscopic Nissen/MGB for large sliding hiatal hernia or paraesophageal hernia between 2013 and 2016. The surgery consisted of a standard MGB combined with crural repair and Nissen fundoplication using the remnant stomach as an anti-reflux valve. During this period, ten patients underwent Nissen/MGB after laparoscopic adjustable gastric band (LAGB) (seven two-stage and three one-stage procedures). None of these patients developed postoperative symptomatic bile reflux.

Our current study, for the first time, investigates the results of applying a similar method for all cases of morbid obesity according to the specified inclusion criteria. Thus, regardless of the presence or absence of insufficiency of the lower esophageal sphincter and hiatal hernia, in the experimental group, we will perform a bariatric surgical procedure, which we called “FundoRingOAGB.” The combination of gastric bypass and fundoplication (CGB&F) as described in the publication can be classified into three main types:
Type 1 CGB&F—One-stage: simultaneous gastric bypass and fundoplication.Type 2 CGB&F—Two-stage: consequent gastric bypass after fundoplication with (a) complete takedown of the wrap; (b) partial takedown of the wrap; and (c) without takedown of the wrap.Type 3 CGB&F—Two-stage: sequential fundoplication after a previous bariatric surgery.Type 1 CGB&F includes primary bariatric procedures, and types 2–3 are secondary surgical procedures [13].

The return of weight after any gastric bypass method significantly reduces the preference for using bariatric and metabolic surgery for the treatment of morbid obesity; therefore, we first examined the likelihood of weight return after the experimental (FundoRingOAGB) and standard procedure of LOAGB. For the primary outcome measure, the change in body mass index will be assessed 12, 24, and 36 months after the surgical procedure.

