Simultaneously, secondary outcome measures were the likelihood of biliary reflux within 12, 24, and 36 months after this procedure. Finally, GERD will be assessed if preoperative GERD symptoms are present or if GERD symptoms occur postoperatively (de novo GERD). For this aim, we will use a quality-of-life scale for gastroesophageal reflux disease (GERD-HRQL) [20].

In the present randomized controlled trial, we expect to show that one anastomosis gastric bypass with fundoplication ring for obese patients will better prevent the return of weight and bile reflux than the standard method. The idea to investigate in a randomized study the combination of two procedures as a primary procedure for one-anastomotic gastric bypass was expressed by [name] [13, 21].

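### Weight regain is in the hypothesis and the primary aim, but no regain measure or contrast is defined, and change from baseline at 36 months cannot by itself separate prevented regain from a larger initial loss

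*Protocol article*

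**What the plan says.** **Aim.** The hypothesis in Objectives {7} is that total fundoplication will, among other things, "significantly prevent the return of weight, such as after banded gastric bypass". The same section gives the primary comparison as "change in body mass index in both groups and weight regain". The Abstract also names preventing regain as the purpose. In the Discussion the authors write that "we first examined the likelihood of weight return after the experimental (FundoRingOAGB) and standard procedure of LOAGB", and they expect to show that bypass with the wrap "will better prevent the return of weight and bile reflux than the standard method".

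**Measurement.** Outcomes {12} says of the primary outcome: "The measure assesses a change of body mass index". The time frame is "Baseline at 12, 24, and 36 months after surgery". Four quantities are listed:
- BMI itself
- ΔBMI, written as "change in BMI (ΔBMI [initial BMI − postoperative BMI" (the bracket closes there)
- excess BMI loss, written as "excess BMI loss (EBMIL, % [(ΔBMI/initial BMI − 25) × 100"
- total weight loss as a percentage of initial weight

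Table 1 schedules BMI before surgery, at operation and at 12, 24 and 36 months, and change in BMI at the three follow-up visits.

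**Analysis.** Statistical methods {20a} compares quantitative variables between groups by one-way ANOVA. It tests within-group change by paired t tests from baseline to each follow-up visit. Sample size {14} rests on postoperative percentage change in BMI.

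**The concern.** Regain is a rise from a value reached after surgery. The three derived measures in {12} all start from the preoperative value, and absolute BMI at a single visit carries no reference point. The Discussion moves directly from weight return to change in BMI at the three visits, as if one measured the other.

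The two can diverge in either direction. A wrap that only increased first-year loss could be reported as preventing regain. A wrap that did prevent regain, but with somewhat less early loss, could look ineffective. The first case is plausible here: {7} likens the wrap to banded bypass, and {6a} describes a similar procedure used to slow the passage of food through the pouch. Such a mechanism could well act on early loss. The headline claim that the Discussion anticipates would then rest on a comparison that does not establish it.

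**Working it through.** **1. What the trial was sized on.** With the constants in {14}, n = 2(1.96 + 1.28)² × 10²/15² = 9.33 per group, as printed. (1.28 is the constant for 90% power, not the stated 80%; that is a separate matter.) The input is postoperative change in BMI. The article gives no SD or target difference for regain.

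**2. Can one 36-month value tell the two mechanisms apart?** The trajectories are assumed, with baseline BMI 40. Excess BMI loss is read as ΔBMI/(initial BMI − 25), and height is constant.

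| Trajectory | BMI at 0 / 12 / 36 months | ΔBMI at 36 | Excess BMI loss | Total weight loss | Regain, 12 to 36 months |
|---|---|---|---|---|---|
| Control | 40 / 28 / 30 | 10 | 10/15 = 66.7% | 10/40 = 25% | 2 (2/12 = 16.7% of loss) |
| Wrap A: regain prevented | 40 / 28 / 28 | 12 | 12/15 = 80% | 12/40 = 30% | 0 |
| Wrap B: larger initial loss | 40 / 26 / 28 | 12 | 12/15 = 80% | 12/40 = 30% | 2 (2/14 = 14.3% of loss) |

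At 36 months A and B are identical on all four listed quantities. Absolute regain is abolished in A and the same as control in B.

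**3. A second case, with equal proportional regain** (also assumed).
- Control 40 → 30 → 32: loss 10, regain 2.0, which is 20% of the loss; 36-month ΔBMI 8.0.
- Wrap 40 → 28 → 30.4: loss 12, regain 2.4, which is 20% of the loss; 36-month ΔBMI 9.6.

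The 36-month difference favours the wrap by 9.6 − 8.0 = 1.6 kg/m², although the wrap arm regains the same share of its loss and 0.4 kg/m² more in absolute terms.

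**4. Scale.** Background {6a} gives typical early loss as 47–80% of excess weight and typical regain as 15–25% of the lost weight. With the ideal of 25 kg/m² used in {12}, excess at BMI 40 is 15.
- Loss: 15 × 0.47 = 7.05 to 15 × 0.80 = 12.0.
- Regain: 7.05 × 0.15 = 1.06 to 12.0 × 0.25 = 3.0 kg/m².

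The 1.6 kg/m² in step 3 lies within the range of the entire regain that the wrap is meant to prevent.

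**5. What a regain contrast could show with 50 per arm.** Assume a loss of 12 units and regain of 15–25% of it (1.8–3.0), halved by the wrap, so that the difference d is 0.9–1.5. Assume complete data and an SD of 2 to 4 for the 12-to-36-month change. The standard error is SD × √(2/50) = 0.2 × SD, the 95% CI half-width is 1.96 × 0.2 × SD, and power = Φ(d/(0.2 × SD) − 1.96).

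| Assumed SD | 95% CI half-width | Power, d = 0.9 | Power, d = 1.5 |
|---|---|---|---|
| 2 | 0.78 | 61% | 96% |
| 3 | 1.18 | 32% | 71% |
| 4 | 1.57 | 20% | 47% |

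**The case against.** **Is every endpoint a change from baseline?** A reader might infer this, but {12} and Table 1 list BMI in its own right, and the reflux endpoints are not weight measures. What stands is narrower: no listed weight measure has a postoperative reference point.

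**Is the trial unable to answer its own question?** This stronger reading also fails. BMI is measured at 12, 24 and 36 months, and 12-to-36-month regain is simply ΔBMI at 12 months minus ΔBMI at 36 months. In step 3 the between-arm difference is 2.0 at 12 months (30 v 28) and 1.6 at 36 months, so the two visits together show the wrap's advantage shrinking. In step 2, A and B already differ by 2 units at 12 months. The planned series separates these cases descriptively. What is lacking is a named variable and a planned comparison, not data.

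**Is this detail that belongs in the full protocol or SAP?** Partly; a regain definition may exist there. But the article does define its primary outcome, with formulas, and its Discussion names change in BMI as the measure for weight return. That is a mismatch between stated aim and stated outcome, not mere brevity.

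**Are the trajectories invented?** Yes. They show that the confusion is possible and could be as large as the effect sought. They do not predict its size in this trial.

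**Conclusion.** The point holds as a mismatch between aim and outcome. Regain is in the hypothesis, the primary aim and the expected conclusion, but it is neither defined nor given a between-arm contrast. A 36-month difference in change from baseline is therefore evidence about net weight loss and does not by itself show prevented regain. Under the assumed trajectories it could favour the wrap by 1.6 kg/m² with no difference in proportional regain, against an implied total regain of 1.06–3.0 kg/m² at BMI 40. The existence of the mismatch follows from the text alone. Its numerical size rests on the assumed trajectories and, for the benchmark, on applying the {6a} percentages to an excess over 25 kg/m².

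**What to change.** **In {12}**, define regain as BMI at 36 months minus BMI at 12 months, in kg/m². Give the percentage of the 12-month loss regained, which is the scale used in {6a}, as a supporting description. One scale has to be fixed in advance because the choice matters: in step 3 the arms differ in kg/m² (2.4 v 2.0) but not as a share of loss (20% in each). Name the visits by month, since Table 1 calls 12 and 36 months V3 and V5, whereas {18a} labels 36 months V4.

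**In {20a}**, add a between-arm comparison of this change in all randomised patients. Report the estimate and 95% CI whatever the change-from-baseline comparison shows. Making it conditional on that result could suppress it in the very case where the wrap prevents regain but gives less early loss.

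**In reporting**, base any statement that the wrap prevents weight regain on this contrast, and describe change from baseline as weight loss.

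**Cost.** A few lines of text, with no new visits or patients. There are two downsides. A nadir before or after 12 months is missed, because no weight visit is scheduled between surgery and 12 months and the reference is fixed at 12 months. The trial was also not sized for regain, so the interval may be wide (step 5), and a non-significant result should not be read as no difference.

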### Trial design {8}

The study was designed as a single-center prospective, interventional, randomized controlled trial. Masking: None (Open Label) Allocation: randomized. Enrollment: 100 obese patients.

## Methods: participants, interventions, and outcomes

### Study setting {9}

Participant data will be collected from “Green Clinic,” Nur-Sultan, Kazakhstan. All operations are performed by one surgeon.

### Eligibility criteria {10}

Inclusion criteria:
Obese patients had a body mass index (BMI) from 30 to 50 kg/m^2^.The patient is generally fit for anesthesia (ASA grading 1–2) and surgery.The patient commits to the need for long-term follow-up.

Exclusion criteria:
Patients with superobesity—BMI more than 50 kg/m^2^.Prosthetic (mesh) Hiatal herniorrhaphy or large hiatal herniaEsophageal shorteningLos Angeles Classification of Esophagitis (LA grade) C or D reflux esophagitisHistory of surgery on the stomach or esophagusLess than 18 or more than 60 years of ageNot fit for bariatric surgeryPsychiatric illnessPatients unwilling or unable to provide informed consent

The drop out criteria:
Refusal to participatePatient not available for long-term follow-up

### Who will take informed consent? {26a}

Written informed consent will be obtained from all participants or their authorized representatives.

### Additional consent provisions for collection and use of participant data and biological specimens {26b}

Not applicable.

## Interventions

### Explanation for the choice of comparators {6b}

The choice of a comparator—the method of laparoscopic one-anastomosis (mini) gastric bypass by M. Carbajo-based long-term follow-up results in 1200 patients [12]

### Intervention description {11a}

Experimental surgical bariatric procedure in the first (A) group: patients (*n*=50) underwent laparoscopic anastomosis (mini) gastric bypass with total wrapping of the fundus of the gastric excluded part and suture cruroplasty if hiatal hernia was present (FundoRingMGB group) (Fig. 1) [13]; active comparator surgical bariatric procedure in the second (B) group: patients (*n*=50) underwent laparoscopic anastomosis (mini) gastric bypass by Carbajo MA (Fig. 2) [14]. Only suture cruroplasty was performed if hiatal hernia was present (LOAGB group).

**Fig. 1 Fig1:**
[figure not shown]
FundoRing OA(M)GB - Laparoscopic anastomosis (mini) gastric bypass with total wrapping of the fundus of the gastric excluded part and suture cruroplasty.© 2021 [name]

**Fig. 2 Fig2:**
[figure not shown]
Laparoscopic one anastomosis (mini) gastric bypass was performed by Carbajo MA© 2021 [name]

### Criteria for discontinuing or modifying allocated interventions {11b}

Not applicable

### Strategies to improve adherence to interventions {11c}

Not applicable

### Relevant concomitant care permitted or prohibited during the trial {11d}

Relevant concomitant care and interventions that are permitted during the trial: using drainage in the abdominal cavity for the first 4 days after surgery.

Relevant concomitant care and interventions are prohibited during the trial: balloon dilatation in the fundoplication area after surgery.

### Provisions for posttrial care {30}

Compensation for those who suffered from participation in the trial is not provided. Elimination of treatment gaps is carried out on a general basis in the national health system.

### Outcomes {12}

#### Primary outcome measure

Change of body mass index: The measure assesses a change of body mass index. Weight (kg) and height (cm) will be combined with the body mass index (BMI) kg/m^2^. Time frame: Baseline at 12, 24, and 36 months after surgery. Ideal body weight was calculated as 25 × [patient’s height in meters]^2^. Effectiveness endpoint follow-up included body mass index (BMI, kg/m^2^), change in BMI (ΔBMI [initial BMI − postoperative BMI]), excess BMI loss (EBMIL, % [(ΔBMI/initial BMI − 25) × 100]), and total weight loss (TWL, % [initial weight − postoperative weight/initial weight × 100]).

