### Sample size {14}

Purpose sampling
Effect size (*d*) (postoperative change in BMI (%)) = 15%.SD = 10.

Formula for calculating sample size is:
$$ n=2\ \left( Z\alpha +Z\left[1-\beta \right]\right)2\times \mathrm{SD}2/\mathrm{d}2 $$

Level of significance = 5%, power = 80% (Sample size increases as power increases. Higher the power, lower the chance of missing a real effect), *Zα* = *Z* is constant set by convention according to accepted α error and *Z* (1-*β*) = *Z* is constant set by convention according to the power of study [16].

Sample size calculations in our study:
$$ \mathrm{Z}\alpha =1.96,\mathrm{Z}\ \left(1-\beta \right)=1.28,\mathrm{SD}=10,\mathrm{d}\ \left(\mathrm{effect}\ \mathrm{size}\right)=15 $$

*n* = 2 (1.96 +   1.28) 2 × 102/152 = 9.33 individuals in each group should be recruited in the study. However, we plan to include more than five times the number of patients in the sample.

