## Statistical methods

### Statistical methods for primary and secondary outcomes {20a}

Statistical analysis will be performed using Microsoft Excel for Mac (Microsoft Corp., Redmond, WA) and StatPlus: MacPro (AnalystSoft Inc., Walnut, CA).

The normal distribution of the variables will be tested using the Kolmogorov–Smirnov test. Subsequently, quantitative demographic and outcome variables will be reported as the means and standard deviations (SD); qualitative variables will be reported as counts and percentages. Between-group comparisons among quantitative variables will be performed using independent one-way ANOVA. Where ANOVA omnibus F test is significant, pairwise comparisons using Fisher's least significant difference (LSD) method will be performed. Between-group differences among qualitative variables will be assessed using the chi-square test or Fisher's exact probability test. Measures of within-group change in quantitative variables, from baseline out to 12, 24, and 36 months, will be analyzed using the dependent-samples *t* test. Correlation and linear regression analyses will be performed to assess the strength and direction of the relationship between changes in BMI and telomere length and to estimate the predictive value of BMI change relative to telomere length at the 12-, 24-, and 36-month follow-ups. Statistical significance was set at *p* < 0.05.

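### Change in BMI is named as the primary outcome, but no primary visit is fixed and its scale differs between sections, so the stated 5% error rate does not hold

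*Protocol article*

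**What the plan says.** All references are to the protocol article.

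- **Primary outcome measure, under Outcomes {12}.** One measure is named first: "Change of body mass index: The measure assesses a change of body mass index". The timing is "Time frame: Baseline at 12, 24, and 36 months after surgery", with no visit singled out. The section defines ΔBMI as initial minus postoperative BMI, an absolute difference in kg/m². It also lists, without rank, BMI itself, percent excess BMI loss (%EBMIL) and percent total weight loss (%TWL), introduced by "Effectiveness endpoint follow-up included body mass index".
- **Objectives {7}.** "Comparing the primary outcome measure: change in body mass index in both groups and weight regain". Weight regain is not defined there or under Outcomes {12}.
- **Discussion.** "For the primary outcome measure, the change in body mass index will be assessed 12, 24, and 36 months after the surgical procedure".
- **Sample size {14}.** The effect size is "postoperative change in BMI" expressed in percent: 15, with SD 10, at a 5% significance level.
- **Statistical methods {20a}.** "Between-group comparisons among quantitative variables will be performed using independent one-way ANOVA", and "Statistical significance was set at" p < 0.05. No order of testing and no adjustment is given.

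**The concern.** A primary outcome needs one variable, one time and one test. Here the variable has a name, but three visits share primary status and the change is absolute in one section and percent in another. Three further weight measures stand beside it with no stated rank. A significant difference at any of the three visits could be reported as the primary result.

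The freedom matters in this trial. It is open label, and Interim analyses {21b} gives the principal investigator access to interim results, so the visit or scale could be chosen by someone who has seen data by arm. The visits also answer different questions. The stated purpose is to prevent weight regain over three years, and an isolated difference at 12 months would not show that, yet nothing in the text stops it from counting.

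**Working it through.** **1. The plan's own figure.** Sample size {14} uses n = 2(Zα + Z(1−β))² × SD²/d² with 1.96, 1.28, SD 10 and d 15:

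2 × (3.24)² × 100/225 = 9.33 per group, as stated.

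The value 1.96 corresponds to one two-sided test at 5%, so the calculation assumes a single primary test. (1.28 is the constant for 90% power, not the stated 80%; that is a separate matter.)

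**2. The scale.** Adult height is fixed, so (BMI₀ − BMIₜ)/BMI₀ = (W₀ − Wₜ)/W₀. The percent change in BMI used for the sample size is therefore the %TWL of the outcome section, not its ΔBMI. The two are not interchangeable. A 15% change is 0.15 × 30 = 4.5 kg/m² at the lower BMI limit for entry and 0.15 × 50 = 7.5 kg/m² at the upper limit.

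**3. Number of comparisons.** Change in BMI at three visits makes 3 tests. Four listed measures at three visits make 12. With two arms, one-way ANOVA is the two-sample t test.

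**4. Reference values if the tests were independent.**

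- 3 tests: 1 − 0.95³ = 14.3%
- 12 tests: 1 − 0.95¹² = 46.0%

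The tests are in fact correlated, so these are upper references.

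**5. Simulation with no treatment effect.**

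- From the document: 50 per arm, BMI range 30-50, SD 10 (given there for the sample size only).
- Assumed: baseline BMI uniform over that range, mean percent loss 30, between-visit correlation 0.5-0.9.

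| Between-visit correlation | ΔBMI, three visits | Any of 12 comparisons |
|---|---|---|
| 0.5 | 12% | 25% |
| 0.7 | 10% | 22% |
| 0.8 | 10% | 21% |
| 0.9 | 8% | 18% |

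A separate simulation took a roughly normal baseline (mean 40, SD 4-5) and a loss SD of 6-10. It gave about 8-13% for ΔBMI at three visits and about 17-25% for all 12 comparisons. The four measures at 36 months alone gave about 10-13%.

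**6. After the fix.** ΔBMI at 36 months alone gave 4.6-5.8% in that second simulation, which is 5% within simulation error.

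**7. Power.** On the plan's own inputs with 50 per group, the standardised difference is 15/(10 × √(2/50)) = 7.5. Power exceeds 99.9% at 0.05, and also at the Bonferroni level for 12 tests, 0.05/12 = 0.0042.

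**The case against.** The strongest reply is that the primary measure is named. Outcomes {12}, the Objectives and the Discussion all say change in BMI, and Table 1 has rows for BMI and its change but none for %EBMIL or %TWL. The four-item list can be read as definitions of derived measures. Statistical methods {20a} gives a general method for quantitative variables; it does not enumerate 12 primary tests. This stands. A reader might infer that the primary outcome is four co-equal measures, or that the false-positive rate simply is about 20%. The document supports neither: nowhere does it say that each listed measure may decide the trial, and the 20% figure needs both that reading and correlations the document does not give.

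A second reply is that this is a journal article, and ranking of supportive measures and multiplicity rules are commonly left to a fuller document. That is fair for the supportive measures. It does not dispose of the point, because the article itself sets the primary outcome, the visits, the sample-size scale and the threshold, and these do not agree on one test.

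A third reply is that percent change at 36 months is not the only sound choice. That is also right. Absolute change would serve, and so would an explicit multiplicity rule over the three visits, for example 0.05/3 = 0.0167 each.

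**Conclusion.** The point holds in this form: change in BMI is the named primary measure, but no primary visit is fixed, its scale is inconsistent between Outcomes {12} and Sample size {14}, and weight regain is added to the primary wording without a definition.

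Followed as written, with any of the three visits able to count, the plan has a false-positive chance of about 8-12% for change in BMI, against the stated 5%. The 14% figure is the bound for independent visits. The range of about 17-25% applies only if any of the 12 listed comparisons is accepted as success.

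The direction does not depend on the assumptions: three imperfectly correlated tests at an unadjusted 0.05 exceed 5% in total. The size does. Apart from the arm size, the BMI range and the SD of 10, the simulation inputs are not in the document.

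**What to change.** - In Outcomes {12} and Statistical methods {20a}, name one primary test: the between-arm difference in change in BMI at 36 months, two-sided 5%. That visit fits the three-year weight-regain aim.
- State one scale, absolute or percent, and use it in Sample size {14} as well. Percent change matches the existing calculation. Absolute change would need an effect and SD restated in kg/m².
- Make the 12- and 24-month results and the other weight measures supportive, reported as estimates with 95% confidence intervals.
- Either define weight regain as a secondary outcome or remove it from the primary wording in Objectives {7}. Change from baseline at 36 months does not by itself measure regain from an earlier low.

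The cost is about a sentence in each section, with no meaningful loss of power on the plan's own assumptions. The downside is that an isolated difference at 12 or 24 months, or on another weight measure, can no longer be claimed as the primary result.

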### Recruitment {15}

We will sample a homogenous population group (obese patients with body mass index (BMI) from 30 to 50 kg/m^2^), thus reducing the standard deviation and hence the sample size. We will recruit 100 obese patients (50 patients in two groups).

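### %EBMIL divides by initial BMI minus 25, so in an unadjusted arm comparison patients near BMI 30 carry disproportionate weight and power is lost for moderate effects (minor)

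*Protocol article*

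**What the plan says.** The Primary outcome measure section of the Protocol article names the outcome: "Change of body mass index: The measure assesses a change of body mass index". It then lists four effectiveness measures: BMI, ΔBMI, total weight loss (%TWL) and "excess BMI loss (EBMIL, % [(ΔBMI/initial BMI − 25) × 100". The printed formula lacks brackets around the denominator. I read it as ΔBMI divided by (initial BMI − 25), the evident intention, and the point below does not depend on that slip.

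Eligibility criteria {10} sets the range: "Obese patients had a body mass index (BMI) from 30 to 50 kg/m^2". Statistical methods {20a} fixes the test: "Between-group comparisons among quantitative variables will be performed using independent one-way ANOVA", with "Statistical significance was set at *p* < 0.05". It names no baseline covariate. Sequence generation {16a} describes 1:1 allocation and no stratification by BMI. Sample size {14} plans on percent change in BMI, "Effect size (*d*) (postoperative change in BMI (%)) = 15" percent, with an SD of 10. It gives no SD for %EBMIL.

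**The concern.** A ratio whose denominator varies fivefold across the eligible population does not weigh patients equally. The same weight loss scores very differently at the two ends of the range, and that spread enters the error term of an unadjusted comparison. If the wrap adds a moderate amount of weight loss to a bypass that both arms receive, %EBMIL could be non-significant while %TWL and ΔBMI, listed beside it, are significant. The article gives no rule for reading such a conflict.

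**Working it through.** **The plan's own figure.** n = 2(1.96 + 1.28)² × 10²/15² = 9.33 per group, as printed. (The stated setting is "Level of significance = 5%, power = 80"%, but 1.28 corresponds to 90%; at 80% the formula gives 6.98. That is a separate matter.) The plan enrols 50 per arm.

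**The scale, from the document alone.** Denominator = BMI₀ − 25.

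| BMI₀ | Denominator | EBMIL points per BMI unit lost | EBMIL at 30% TWL |
|---|---|---|---|
| 30 | 5 | 20 | 180% |
| 35 | 10 | 10 | 105% |
| 40 | 15 | 6.7 | 80% |
| 50 | 25 | 4 | 60% |

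The last column is 30 × BMI₀/(BMI₀ − 25). The per-unit weight differs fivefold between the ends of the range, or 25-fold in variance.

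**Power, by hand for one case.** Assumptions not in the protocol: TWL mean 30% in control and 35% with the wrap, SD 8, independent of BMI₀; BMI₀ uniform on 30–50; 50 per arm; two-sided 5% (critical t on 98 df = 1.984).

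- EBMIL = TWL × g, with g = BMI₀/(BMI₀ − 25) = 1 + 25/u and u uniform on 5–25.
- E[g] = 1 + 25 ln(5)/20 = 3.012. E[g²] = 1 + 50 ln(5)/20 + 625(1/5 − 1/25)/20 = 10.024.
- Control variance = (30² + 8²) × 10.024 − (30 × 3.012)² ≈ 1,499 (SD 38.7). Wrap variance = (35² + 8²) × 10.024 − (35 × 3.012)² ≈ 1,809 (SD 42.5).
- Mean difference = 5 × 3.012 = 15.06. SE = √((1,499 + 1,809)/50) = 8.13. Ratio 1.85, power about 45%.
- %TWL: SE = 8√(2/50) = 1.6; 5/1.6 = 3.125; power about 87%.
- ΔBMI: difference 5% × 40 = 2.0 units; SE 0.748; ratio 2.67; power about 75%.

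**Simulation across baseline mixes** (same TWL assumptions, 8,000 trials per row, Monte Carlo 95% error about ±1 point; normal mixes have SD 5 and are truncated to 30–50):

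| BMI₀ mix | EBMIL, unadjusted | ΔBMI | %TWL | EBMIL adjusted for BMI₀ |
|---|---|---|---|---|
| Uniform 30–50 | 46% | 76% | 87% | 75% |
| Normal, mean 38 | 57% | 80% | 87% | 80% |
| Normal, mean 40 | 59% | 80% | 87% | 80% |
| Normal, mean 42 | 64% | 82% | 88% | 82% |

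- *Influence of the lightest patients.* Those below BMI 35 supply 61% of within-arm EBMIL variance when they are 25% of the sample (uniform), 47% when they are 14% (mean 40) and 36% when they are 8% (mean 42).
- *Discordance.* %TWL is significant and EBMIL is not in 43%, 32%, 29% and 24% of trials, in the order of the rows.
- *The protocol's SD of 10, still with a 5-point difference.* EBMIL 39–53% against 69–70% for %TWL.
- *The protocol's planning effect, 15 points with SD 10.* By hand for the uniform mix: 45.18/9.79 = 4.6, power above 99%. Simulated: 99.7% to 100%. At 10 points: 90–98%.
- *Type I error with no arm difference.* 4.2–5.2%.

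**The case against.** The strongest reply is that the trial's main question is untouched. Change in BMI is the named primary outcome. The schedule of assessments lists only BMI and its change as weight measures. BMI, ΔBMI and %TWL carry no such denominator. At the effect the protocol plans for, %EBMIL misses nothing; the low power figures belong to a difference one third as large, which the document does not state. Covariate adjustment of a supporting measure may also be in an analysis plan that is not shown. All of this stands, and it makes the point minor. What survives is that the article lists the measure under the primary outcome and fixes an unadjusted test for quantitative variables.

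A reader might go further in four ways that the document does not support:

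- *Chance imbalance in light patients could produce a false wrap effect.* Randomisation and a valid two-group test already account for such imbalance, and the error rate stays near 5%.
- *The eligible range creates the larger part of the EBMIL variance.* At SD 8, baseline BMI accounts for 57% of it under a uniform mix but only about 38–46% under the normal mixes. The protocol gives no mix.
- *The Recruitment {15} statement about a homogeneous population, "thus reducing the standard deviation and hence the sample size", is refuted.* It supports a sample size set on percent change in BMI, not on %EBMIL, so no change to it follows.
- *Values above 100% are rewarded as success.* The article defines no success threshold on %EBMIL.

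**Conclusion.** The point holds as a minor one. The fivefold difference in weighting is exact arithmetic from the protocol's formula and eligibility range. For moderate effects (about 3 to 6 TWL points), the unadjusted comparison of %EBMIL has clearly less power than the measures beside it: about 45–65%, against 87–88% for %TWL and 75–82% for ΔBMI, at a 5-point difference with SD 8. The gap was present in every baseline mix tried and widest when many patients are near BMI 30. These power figures rest on the assumed TWL distribution, its independence from baseline BMI and the assumed mixes; only the sample size and alpha come from the document. The document does not support a reading that the trial would miss a weight effect on its primary outcome.

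**What to change.** In Primary outcome measure and Statistical methods {20a}, name %TWL as the tested relative weight-loss measure. At constant height it equals percent change in BMI, which is the scale of the sample size calculation, and it is already listed. Report %EBMIL descriptively by initial BMI class, for example 30 to <35, 35 to <40 and 40 to 50. If a test of %EBMIL is wanted, include baseline BMI as a covariate; under the same assumptions this restores power to about 75–83%, close to that of ΔBMI, so the test need not be banned.

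The cost is wording in two sections and no new data. The small downside is that there is no unadjusted p-value for %EBMIL; the descriptive table keeps the measure available for comparison with other reports.
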